**2. Secondary endpoints and indicators**

2.1 Incidence and rate of hypoglycemia;

2.2 General efficacy (FPG, 2hPG, HbAlc) and the efficacy of TCM Syndrome of dual deficiency of *qi* and *yin* ;

2.3 Proportion of patients with HbA1c < 6.5% at 48 week;

2.4 The time to achieve HbA1c <6.5%;

2.4 Changes in islet -cell function (HOMA-IS = 20 × FINS/(FPG-3.5));

2.5 Changes in insulin resistance levels (HOMA-IR = FINS × FPG/22.5);

2.6 Changes in weight, waist circumference, and hip circumference;

2.7 Changes in lipids levels, insulin levels, inflammatory factors (hsCRP), and adiponectin;

2.8 Metabolomics and pharmacogenetics;

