**5. Termination (withdrawal)**

In the following situations, the study will be terminated for the patients, but the patients will be included in the FAS statistics:

5.1 If the female patient gets pregnant (violation to the protocol).

5.2 If the patient has not used the study drugs (including metformin) in accordance with therequirements of the protocol for more than 7 consecutive days.

5.3 If the patient has used insulin for more than 7 days, or month than 7 days within 1 month.

5.4 If the patient has used combined therapy with the drugs that should be excluded for more than 7 days.

5.5 If the patient’s (finger whole blood) fasting blood glucose has been greater than 234 mg/dL (13 mmol/L) for 3 consecutive times (lack of efficacy).

5.6 Serious adverse events occur.

5.7 If the patient has recurrent hypoglycemia (more than 2 episodes of hypoglycemia per week in 4 consecutive weeks), especially severe hypoglycemia (more than 2 episodes of severe hypoglycemia within 30 days), the investigator must consider terminating the trial for the patient.

If the investigators determine the patients should withdraw from the trail because of serious adverse events or significantly increased clinical laboratory parameters, appropriate measures should be taken immediately and the principal of the study should be notified.

The investigators terminate the trial or terminate the patients to participate in the trial for any reason; those patients under early termination will continue to carry out the visit procedures for early termination as specified in the protocol procedures.

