## X. Adverse events

**1. Definition**

1.1 Adverse Events: refer to adverse medical events occur after patients or subjects of clinical trials treated with a drug, which do not necessarily have a causal relationship with the treatment.

1.2 Serious adverse events: events occurred during clinical trials requiring hospitalization, prolonged length of hospital stay, disability, affecting the work ability, endangering the life or leading to death, resulting in congenital malformations.

1.3 Adverse drug reactions: refer to harmful, unexpected reactions which have a causal relationship with the application of the drug occurred during the process of normal application of a drug at a dose in line with the requirements. In a clinical trial of a new drug or new usage of a drug, when the therapeutic dose has not been established, all the harmful, unexpected reactions which have a causal relationship with the application of the drug should be considered as adverse drug reactions.

1.4 Hypoglycemia: patients with hypoglycemia will record the episodes of hypoglycemia, blood glucose levels, concomitant symptoms and the treatment in the study diary card provided by the sponsor.

1.4.1 The episode of hypoglycemia is defined as the patient feel that he/she has the signs or symptoms associated with hypoglycemia at any time, or with blood glucose <63 mg/dL (3.5 mmol/L) [IFCC  plasma:<68 mg/dL (3.8 mmol/L))], even if not accompanied by symptoms, signs or not requiring treatment.

1.4.2 Severe hypoglycemia is defined as the patient has onset of symptoms related to hypoglycemia and need help from others, with blood glucose < 50 mg/dL (2.8 mmol/L) [IFCC plasma: <55 mg/dL (3.0 mmol/L) ] or immediately recovered after oral administration of carbohydrate or glucagon or intravenous injection of glucose.

1.4.3 The definition on blood glucose levels of nocturnal hypoglycemia is similar (for example: hypoglycemia is <63 mg/dL, severe hypoglycemia <50 mg/dL), which is according to the adverse event reports and blood glucose levels of the patients. Nocturnal hypoglycemia is defined as the event that occurs before the 1st meal (e.g. breakfast) after wake up from falling sleep.

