**Classification of hypoglycemic reactions:**

| **Classification** | **Clinical manifestation** | **Treatment** |
| --- | --- | --- |
| Hypoglycemia | Tachycardia, palpitations, trembling, sweating, hunger, dizziness, blurred vision, impaired concentration, behavior disorders, etc. Patients do not need assistance from others, and can take the initiative to seek treatment. Or blood glucose <63 mg/dL (3.5 mmol/L) [IFCC plasma :< 68 mg/dL (3.8 mmol/L)], even if not accompanied by symptoms, signs or not requiring treatment. | Rapid remission after eating carbohydrates |
| Severe hypoglycemia | Hypoglycemia leads to manifestations such as coma, seizures or nervous system damage, and the patient cannot take the initiative to require treatment or seek help. Accompanied by blood glucose < 50 mg/dL (2.8 mmol/L) [IFCC plasma: < 55 mg/dL (3.0 mmol/L)] | Requiring intravenous bolus injection of glucose or glucagon injection for emergency treatment |
| Nocturnal hypoglycemia | Nocturnal hypoglycemia refers to the event that occurs before the 1st meal (e.g. breakfast) after wake up from falling sleep, presenting with clinical manifestations and blood glucose values of hypoglycemia or severe hypoglycemia | Mild patients should take food, while severe patients need intravenous injection of glucose |

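### Severe hypoglycaemia is defined in two conflicting ways, so the severe/non-severe split and the severe count in termination item 5.7 can depend on which definition a site uses

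*Protocol*

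**What the plan says.** Section X of the protocol deals with hypoglycaemia in two adjacent places.

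- **Item 1.4.1** defines an episode as symptoms or signs felt by the patient, or a glucose below 63 mg/dL even without symptoms. It sets no condition on assistance.
- **Item 1.4.2** defines severe hypoglycaemia: "the patient has onset of symptoms related to hypoglycemia and need help from others", with glucose below 50 mg/dL or immediate recovery after oral carbohydrate, glucagon or intravenous glucose.
- **The table of hypoglycaemic reactions, severe row,** reads "Hypoglycemia leads to manifestations such as coma, seizures or nervous system damage". It adds that the patient cannot ask for treatment or help and that glucose is below 50 mg/dL. Its treatment column reads "Requiring intravenous bolus injection of glucose or glucagon injection for emergency treatment".
- **The table's ordinary row** admits symptomatic episodes on the condition "Patients do not need assistance from others, and can take the initiative to seek treatment", or any episode with glucose below 63 mg/dL.

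The classes are used elsewhere. Section III.2 lists "Incidence and rate of hypoglycemia" as the first secondary endpoint, without naming a severity. Section V.5, item 5.7, uses "more than 2 episodes of severe hypoglycemia within 30 days" as a ground on which the investigator must consider ending a patient's participation. Section XII.8 leaves the between-group comparison of hypoglycaemia to the statistical analysis plan. The case definition itself is fixed in Section X.

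**The concern.** The two severe definitions differ on three elements: the clinical threshold, whether a low reading is mandatory, and whether recovery on oral carbohydrate can qualify. No sentence ranks one above the other, and Section IV.6 lists 18 centres that will classify episodes as they occur.

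Three things are at stake. First, a table of severe events by arm would mix two case definitions. Second, item 5.7 could be triggered for a patient at one centre and not for an identical patient at another. Third, a centre that uses the table to decide what counts as an episode would have no row for some assisted episodes. Hypoglycaemia matters here: goal 2.2 in Section II calls it the main side effect and makes it a target for biomarker work.

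**Working it through.** The protocol states no event rate, power or sample size for hypoglycaemia (the calculation in Section IV.1 concerns HbA1c), so there is no figure to reproduce. The check is a comparison of the rules.

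| Element | Item 1.4.2 | Table, severe row |
| --- | --- | --- |
| Clinical state | Symptoms, needs help from others | Coma, seizure or nervous system damage (given as examples); cannot seek help |
| Glucose below 50 mg/dL | One of two alternatives | Accompanies the episode; no alternative |
| Recovery on oral carbohydrate | Qualifies | Not listed |
| Intravenous glucose or glucagon | Qualifies through recovery | Listed as the treatment |

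**Enumeration.** Take symptomatic episodes in which the patient needed help, and cross:

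- 2 clinical states: coma or seizure and unable to seek help; needs help only.
- 4 glucose states: below 50, 50 to 62, 63 or more mg/dL, not measured.
- 3 responses: prompt recovery on oral carbohydrate; prompt recovery on intravenous glucose or glucagon; no prompt recovery.

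This gives 2 × 4 × 3 = 24 types.

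- **Severe under 1.4.2.** Glucose below 50: 2 × 1 × 3 = 6. Other glucose states with prompt recovery: 2 × 3 × 2 = 12. Total 18.
- **Severe under the table** by clinical state and glucose: 1 × 1 × 3 = 3. If the treatment column also binds: 1 × 1 × 1 = 1.
- **Disagreement.** Every type that is severe in the table is severe under 1.4.2, so the definitions differ on 18 − 3 = 15 types, or 18 − 1 = 17 with the treatment column.
- **Lenient reading of the table.** Suppose the neurological signs are only examples and inability to seek help is taken as equivalent to needing help. The table then gives 2 × 1 × 3 = 6 severe types, and the definitions still differ on 18 − 6 = 12, because the low reading remains mandatory.
- **No row in the table.** Assisted episodes with no reading or a reading of 63 mg/dL or more: 2 × 2 × 3 = 12 types fit neither the severe nor the ordinary row. All 12 are hypoglycaemia under 1.4.1, and 2 × 2 × 2 = 8 of them are severe under 1.4.2.

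These are counts of logical types, not expected frequencies.

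**Effect on item 5.7.** Suppose a conscious patient has three assisted episodes within 30 days, each with a reading of 55 mg/dL and prompt recovery on oral carbohydrate. Under 1.4.2 that is three severe episodes, which exceeds two. Under the table it is three ordinary episodes, through the glucose route, and no severe ones.

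**Effect on endpoint 2.1.** Under 1.4.1 all 24 types count as hypoglycaemia, so moving an episode between severe and non-severe leaves the overall count unchanged. The count changes only for the 12 types without a row, and only if a site applies the table in place of 1.4.1.

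**The case against.** The strongest reply is that endpoint 2.1 concerns hypoglycaemia overall, that 1.4.1 defines it without regard to severity, and that no severe-hypoglycaemia endpoint is listed. This stands. It limits the point mainly to the severity split and item 5.7.

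Second, the table can be read more loosely: its neurological signs are examples, and a treatment column need not be a case criterion. This narrows the conflict but does not remove it, since the mandatory low reading still leaves 12 of 24 types in dispute.

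Third, randomisation is stratified by centre and the trial is double-blind (Sections IV.2 and IV.4), so differing site habits should fall about equally on both arms. That is a fair reason to expect noise rather than systematic bias between arms.

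Fourth, the analysis plan could impose one definition at analysis. This is partly right: the diary (X.1.4) captures glucose, symptoms and treatment, and the case report form (X.2) captures degree and course. Neither list names help from others, on which 1.4.2 turns, so reclassification is not assured. Item 5.7 is applied during the trial, where a later plan cannot help.

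A reader might also infer that the definition could be chosen once treatments are known. Section IV.5.3 does not support that: data are locked first, the statistician receives only codes A and B, and treatments are disclosed after the statistical report is complete.

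**Conclusion.** The contradiction is explicit and should be resolved. The severe/non-severe split, and the severe count used in item 5.7, can differ between sites. That they will differ is an inference, since the documents do not show which definition sites will use. The primary HbA1c endpoint is not touched.

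Three stronger readings are not supported:

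- **That endpoint 2.1 as a whole will be miscounted.** It is affected only where the table replaces 1.4.1.
- **That some assisted episodes have no class in the protocol.** The gap lies inside the table, and assisted episodes with a reading below 63 mg/dL do have a row there.
- **That the excess of severe events can be sized, or that the difference between arms could change sign.** One might write the ratio of severe counts as 1/(1 − q), with q the share of assisted episodes without coma or seizure. For q from 0.3 to 0.7 this gives 1.4 to 3.3. But q is assumed, the documents give no value, and the formula ignores the glucose condition. No calculation supports a change of sign.

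No size of effect can be derived from the documents.

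**What to change.** 1. Reconcile item 1.4.2 and the table into one severe definition. Its content is for the clinical team to choose. Use it for both severity reporting and item 5.7.
2. State that 1.4.1 is the case definition for endpoint 2.1.
3. Make the table's severity classes exhaustive and mutually exclusive: assess severe first, and class every other 1.4.1 episode as non-severe. Deleting the no-assistance condition alone would not do, because the two rows would then overlap.
4. Record need for assistance, coma or seizure, glucose value and treatment as separate diary or case report form fields, so that one definition can be applied uniformly. Glucose and treatment are already collected; need for assistance is the element not named.

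The cost is table wording and a few diary or case report form fields.

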**Study Termination Criteria**

When fasting blood glucose is found to exceed 126 mg/dl (7.0 mmol/L) for the first time after Xiaoke Pills is administered reaching a dose of 30 pills/day or glibenclamide is administered reaching a dose of 3 tablets/day, if the fasting plasma glucose level is still below 200 mg/dl (11.1 mmol/L), the patient may be observed continuously till the next follow-up. During this period, the patient is told to test blood glucose at home by him/herself, if fasting blood glucose (finger whole blood) exceeds 234 mg/dL (13 mmol/L) on 2 consecutive testing, the patient should withdraw from the study and receive conventional treatment.

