## V. Case selection criteria

**1. Inclusion criteria**

1.1 Patients with type 2 diabetes;

1.2 Belonging to TCM Syndrome of dual deficiency of *qi* and *yin*;

1.3 Aged 21～70 years;

1.4 Patients for initial treatment: Patients who have not received any hypoglycemic agent and are non-obese,, with body mass index (BMI) within 18kg/m2 ~ 28 kg/m2 (not included);

1.5 Patients treated with metformin: Patients have received treatment with metformin (immediate-release) at a stable dose ≥ 750 mg/day for at least 3 months before screening, with body mass index (BMI) within 18kg/m2 ~ 35 kg/m2 (not included);

1.6 Body weight remains constant (body weight fluctuates by less than 10% within at least 3 months before screening);

1.7 Poor glycemic control, fasting blood glucose greater than 126 mg/dl (7.0 mmol/L) and HbA1c >7.0% (preliminary screening), fasting blood glucose greater than 126 mg/dl (7.0 mmol/L) (after run-in);

1.8 Patients still meet the above criteria (without considering HbA1c) after a 4-week run-in period.

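### The plasma cut-off for severe hypoglycaemia is printed as 55 mg/dL (3.0 mmol/L), two limits about 1 mg/dL apart, so a plasma reading of 3.0 mmol/L meets one and not the other

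*Protocol*

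**What the plan says.** Section X, item 1.4.2 of the protocol defines severe hypoglycaemia as symptoms with a need for help from another person, together with one of two conditions. The first is a glucose limit, given for blood as "with blood glucose < 50 mg/dL (2.8 mmol/L") and for plasma as "IFCC plasma: <55 mg/dL (3.0 mmol/L"). The second is immediate recovery after oral carbohydrate, glucagon or intravenous glucose.

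The table classifying hypoglycaemic reactions repeats the plasma pair as "IFCC plasma: < 55 mg/dL (3.0 mmol/L"). There the glucose value accompanies coma, seizures or nervous system damage, and recovery is not offered as an alternative.

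Neither place says whether mg/dL or mmol/L governs. Item 1.4.3 restates the severe limit for nocturnal events in mg/dL only, using the blood figure of 50.

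The severe class is used again in section V.5, item 5.7, where "more than 2 episodes of severe hypoglycemia within 30 days" is a ground on which the investigator must consider ending the trial for that patient.

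**The concern.** A cut-off printed in two units should classify a given reading the same way in both. This one is a strict less-than limit, and its two printed values differ by more than rounding explains. The other paired glucose thresholds in the trial rules agree after rounding, so the protocol's practice is to round, and this pair departs from it. The same pair stands in two separate places, so it is unlikely to be a slip in extracting the text.

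What is at stake is whether an episode with a plasma reading at the limit is called severe. Under the table the glucose value is required, so there the choice of unit could settle the class. That class then enters the count of severe episodes considered under item 5.7.

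**Working it through.** **Inputs.** All glucose pairs are from the protocol: section X items 1.4.1 and 1.4.2 and the classification table; the Study Termination Criteria in section III; and the inclusion criteria in section V.1.

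**Conversion.** mmol/L = (mg/dL) / f. The protocol's own pairs "fasting blood glucose greater than 126 mg/dl (7.0 mmol/L") and "exceeds 234 mg/dL (13 mmol/L") give f = 126/7.0 = 18.0 and f = 234/13 = 18.0. The check was repeated with f = 18.016, from a molar mass of glucose of about 180.16 g/mol; this value is an outside constant, not in the protocol.

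**Step 1: does each printed pair reproduce?**

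| Pair (mg/dL, mmol/L) | mg/dL ÷ 18.0 | mg/dL ÷ 18.016 | At one decimal | Agrees |
| --- | --- | --- | --- | --- |
| 63, 3.5 (hypoglycaemia, blood) | 3.500 | 3.497 | 3.5 | yes |
| 68, 3.8 (hypoglycaemia, plasma) | 3.778 | 3.774 | 3.8 | yes |
| 50, 2.8 (severe, blood) | 2.778 | 2.775 | 2.8 | yes |
| **55, 3.0 (severe, plasma)** | **3.056** | **3.053** | **3.1** | **no** |
| 126, 7.0 | 7.000 | 6.994 | 7.0 | yes |
| 200, 11.1 | 11.111 | 11.101 | 11.1 | yes |
| 234, 13 | 13.000 | 12.988 | 13.0 | yes |

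Only truncation turns 55 mg/dL into 3.0 mmol/L, and truncation would have broken other pairs: 3.778 would become 3.7 and 2.778 would become 2.7.

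**Step 2: the reverse direction.** 3.0 × 18.0 = 54.0 mg/dL and 3.0 × 18.016 = 54.05 mg/dL. Both give 54, not 55.

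**Step 3: the zone of disagreement.** The two limits part from 3.00 mmol/L up to 55/18.016 = 3.053 mmol/L (55/18.0 = 3.056). That is a width of about 0.05 mmol/L, or 55 − 54 = 1 mg/dL.

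**Step 4: what that means for a recorded value.** Take a plasma reading of 3.0 mmol/L, which is 54.0 to 54.05 mg/dL.
- Against 55 mg/dL: 54.0 < 55, so the limit is met.
- Against 3.0 mmol/L: 3.0 is not below 3.0, so the limit is not met.

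On a one-decimal mmol/L scale this is the only value affected: 2.9 is below both limits (2.9 × 18.0 = 52.2) and 3.1 is below neither (3.1 × 18.0 = 55.8). The other hypoglycaemia pairs do not split such a reading. For example, 2.8 × 18.0 = 50.4 is not below 50, and 2.8 is not below 2.8.

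**Step 5: effect on the total count.** Item 1.4.1 counts any symptomatic episode and any plasma value meeting "<68 mg/dL (3.8 mmol/L"). A reading of 3.0 mmol/L (54 mg/dL) is below 3.8 mmol/L and below 68 mg/dL, so it counts as hypoglycaemia in either unit.

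**The case against.** The case against giving this weight is strong, and most of it stands.

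- **It is a rounding slip.** At f = 18.016, 55 mg/dL is 3.053 mmol/L, only 0.003 above the point where one-decimal rounding changes from 3.0 to 3.1. That is so, but the limit is a strict inequality and the reading of 3.0 mmol/L falls in the gap.
- **The endpoint is untouched.** A reader might infer that the hypoglycaemia endpoint would be miscounted. Secondary endpoint 2.1 is the incidence and rate of hypoglycaemia with no severe category named, and Step 5 shows that the disputed reading counts either way. Only a severity sub-class can move.
- **Glucose is not the only route.** Under item 1.4.2 an assisted episode that recovers immediately after treatment is severe whatever the reading. This stands for item 1.4.2. It does not help under the table, which gives no such alternative.
- **Whole-blood values are unaffected.** Home testing for the withdrawal rules is described as finger whole blood, and the blood pair of 50 and 2.8 is consistent. The protocol does not describe sites mixing units or meter calibrations, so it does not support saying that centres will classify differently; they could.
- **Item 5.7 is a judgement.** A reader might infer that the slip triggers or blocks withdrawals. The item obliges the investigator to consider termination, and the slip matters only if one of the episodes in the count has the disputed reading and no other route to the severe class applies.

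The same definition applies to both arms of a double-blind trial, so the document gives no reason to expect a bias between them.

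**Conclusion.** The inconsistency is real and minor. The plasma limit for severe hypoglycaemia is stated as two values about 1 mg/dL (0.05 mmol/L) apart, in two places, with no governing unit. In practice it concerns a plasma reading recorded as 3.0 mmol/L. It could decide the class mainly under the table, and through that could alter the number of severe episodes considered under item 5.7. It does not affect the total count in endpoint 2.1, the primary HbA1c comparison or the sample size.

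The conversion rests on f between 18.0 and 18.016, and the result is the same across that range. No proportion of reclassified episodes is offered, because the protocol gives no distribution of glucose values in severe episodes.

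**What to change.** Make the mg/dL and mmol/L figures of the plasma limit agree in section X item 1.4.2 and in the classification table. State which unit governs, and derive the severe class in the database from the recorded glucose in that unit. The clinical team decides which cut-off is meant; the arithmetic shows only that the two printed figures cannot both be the limit.

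The cost is one figure corrected in two places and one added sentence on the governing unit, carried through the Ethics Committee approval that section XIII requires for any protocol amendment. Nothing in the design, sample size or primary analysis changes.

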**Classification of hypoglycemic reactions:**

| **Classification** | **Clinical manifestation** | **Treatment** |
| --- | --- | --- |
| Hypoglycemia | Tachycardia, palpitations, trembling, sweating, hunger, dizziness, blurred vision, impaired concentration, behavior disorders, etc. Patients do not need assistance from others, and can take the initiative to seek treatment. Or blood glucose <63 mg/dL (3.5 mmol/L) [IFCC plasma :< 68 mg/dL (3.8 mmol/L)], even if not accompanied by symptoms, signs or not requiring treatment. | Rapid remission after eating carbohydrates |
| Severe hypoglycemia | Hypoglycemia leads to manifestations such as coma, seizures or nervous system damage, and the patient cannot take the initiative to require treatment or seek help. Accompanied by blood glucose < 50 mg/dL (2.8 mmol/L) [IFCC plasma: < 55 mg/dL (3.0 mmol/L)] | Requiring intravenous bolus injection of glucose or glucagon injection for emergency treatment |
| Nocturnal hypoglycemia | Nocturnal hypoglycemia refers to the event that occurs before the 1st meal (e.g. breakfast) after wake up from falling sleep, presenting with clinical manifestations and blood glucose values of hypoglycemia or severe hypoglycemia | Mild patients should take food, while severe patients need intravenous injection of glucose |

